**Methods/design:**

We will conduct a single-blind randomised clinical trial to compare three different 8 week rehabilitation programs: Group 1 will receive education on symptoms management based on training modifications; Group 2 will receive an exercise program targeting lower limb strengthening and control in addition to the education component of Group 1; Group 3 will receive running gait retraining advice as well as the education component of Group 1. Sixty-nine runners with PFP will be recruited and will be seen by independent physiotherapists on five visits through 8 weeks. The primary outcome measure will be symptoms and functional limitations measured by the Knee Outcome Survey – Activities of Daily Living Scale questionnaire at baseline, and at the four, eight and 20 weeks follow-up. Secondary outcomes will include pain level measured using visual analog scales, and running mileage. Lower limb kinematics and kinetics during running, and isometric strength will also be evaluated at baseline and 8 weeks follow-up. The effects of rehabilitation programs on measures of symptoms and functional limitations will be assessed using a 2-way ANOVA (Groups x Time). Regression analyses will be used to identify if changes in running mechanics or strength are determinants of clinical success.

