## Methods/design

### Study design

This stratified, single-blind, parallel-group randomised clinical trial will include four evaluation sessions (baseline, week 4, week 8, week 20) and five supervised physiotherapy sessions during an 8 week rehabilitation program. The evaluation sessions will be carried out at the Centre for Interdisciplinary Research in Rehabilitation and Social Integration (CIRRIS) in Quebec City, Canada. The supervised physiotherapy treatments will be conducted at the *Clinique de physiothérapie PCN La Capitale*, a private clinic specialised in the treatment of running injuries. Runners will be allocated to either 1- an intervention that will only include education and training modifications according to symptoms; 2- the addition of a strengthening and lower limb control exercise program to the education component; 3- modifications to the running gait in addition to the education component.

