### Procedures

All included runners will take part in the baseline evaluation session. First, questionnaires on sociodemographic, symptomatology, comorbidity, and running habits will be completed. Thereafter, the level of symptoms and functional limitations will be evaluated using self-reported questionnaires (KOS-ADLS and visual analog scales), before assessing knee and hip muscle strength. Then, lower limb kinematics and kinetics will be evaluated while running on an instrumented treadmill. Finally, runners will be randomly assigned to one of the three intervention groups, and will take part in their assigned 8 week rehabilitation program.

At weeks 4, 8, and 20 (3 months following completion of the program), self-reported questionnaires completed at baseline will be re-administered. This will allow us to determine if a program leads to a faster recovery and to better long-term effects. At week-8 evaluation, lower limb mechanics during running and strength will also be revaluated in the laboratory. All runners will be provided with a GPS-enabled watch (Garmin Forerunner 15) so that running mileage, speed, duration and step count are monitored during the intervention period.

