#### Running mileage

Runners’ training will be monitored using a GPS-enabled Garmin Forerunner 15 watch. Weekly running mileage will be made available to researchers using an online log, and will allow us to assess changes in training volume during the 8 week intervention.

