### Rehabilitation programs (independent variables)

Each runner will take part in one of three rehabilitation programs carried out over five sessions by independent physiotherapists. A training session will be performed prior to recruitment to ensure standardisation of the intervention between the physiotherapists, and detailed documents reviewing the content of each meeting will be provided. Furthermore, frequent follow-ups will be made by the research team with the physiotherapists to ensure the consistency of program delivery. Runners will receive written instructions, and, when applicable, pictures illustrating the exercises. All components of each intervention will be addressed at every visit to the clinic. During the programs, participants will continue to run.A)*Education group*This group will receive a program that will only include the same education component on symptoms management that the two other groups will receive. Runners will be asked to run more often, but to decrease daily distance and running speed as well as to avoid downhill running. They will be instructed to maintain patellofemoral pain level at a maximum of 2/10 during running. In addition, pain should return to before-training levels within 60 min post training. Gradually, running distance will be increased according to symptoms, up to baseline level or more, before adding speed and hills [30].B)*Exercise group* (strengthening and lower limb control)In addition to the education on symptoms management, runners will be asked to perform a standardised exercise program focusing on strengthening and lower limb control three times per week. The same exercise program was used in a previous study from our research group [30]. Each exercise session will last a maximum of 20 min. Exercises will be gradually progressed through higher difficulty levels of knee/hip/core strength and lower limb control including jumps and elastic bands. Exercises will be individually dosed and progressed by the treating physiotherapist. No recommendation about lower limb alignment during running will be provided.C)*Gait retraining group* (reducing impact forces)In addition to education on pain management, runners will receive personalised advice on running mechanics in order to reduce patellofemoral joint load. Specifically, step rate will be increased, and noise produced during running will be decreased so that vertical ground reaction forces are reduced [28, 29, 49–51]. Runners for whom noise reduction will not be an efficient strategy will be asked to modify their foot strike pattern to midfoot or forefoot [31]. We decided to use the approach targeting decreased ground reaction forces since it is applicable to a vast majority of runners, compared with the kinematics approach which has only been tested in runners with excessive hip adduction [32, 34].

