
Sample size calculation and statistical analyses: Sample size calculation is based on changes to KOS-ADLS scores, our primary outcome, which are expected to increase following the different interventions. In a previous study using an 8 week multimodal intervention program similar to the current study, KOS-ADLS scores increased from 71.7 ± 12.9 to 89.5 ± 11.9 [30]. Considering similar score changes to our primary outcome, α = 0.05, power of 90 % and CID of 13.6 points for the KOS-ADLS, 20 runners are needed in each group (G*Power 3.1.7). When adding an anticipated attrition rate of 15 %, 23 runners per group are needed; therefore, a total of 69 runners will be recruited. Baseline demographic data will be compared (one-way ANOVA and Chi-squared tests). If baseline characteristics are different across groups, we will adjust group comparisons for confounding variables using an ANCOVA model. An intention-to-treat analysis will be used in which all participants will be analysed in the group to which they were originally assigned, up to the 8 week point. Dropouts or loss to follow-up will not be carried forward to the 3 month follow-up, since a successful outcome after 8 weeks may not necessarily be maintained 3 months later. This will avoid false assumptions regarding durable benefits from the intervention. Per protocol analyses (i.e., analyses restricted to patients who received the intervention as intended) will also be performed. All dropouts and reasons underlying dropouts will be reported. If requested, subjects electing to drop-out will be referred to their treating physician for other treatment options. Any harms or unintended effects during the course of the rehabilitation programs will be reported and discussed. For objective one, a 2-way ANOVA (Groups x Time) will be used to analyse the effects of the rehabilitation programs on KOS-ADLS, VASs and running mileage. For objective two, logistic regression analyses will be performed to identify if changes in running mechanics or strength are determinants of clinical success. For these analyses, results to KOS-ADLS will be dichotomised to changes equal or superior to the CID of 13.6 points, or to changes inferior to this value [36]. Subjective success will also be dichotomised to GRC ≥ +5 or GRC < +5.

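### Harms and watch-recorded running load are followed only during the 8-week programs, while benefit is judged to week 20

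*Protocol article*

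**What the plan says.** **Harms.** The paragraph on sample size and statistical analyses, at the end of the Rehabilitation programs section, states: "Any harms or unintended effects during the course of the rehabilitation programs will be reported and discussed". Study design gives the length of those programs: "five supervised physiotherapy sessions during an 8 week rehabilitation program".

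**Running load.** Under Procedures, each runner receives a GPS watch "so that running mileage, speed, duration and step count are monitored during the intervention period". The Running mileage section says that the weekly log "will allow us to assess changes in training volume during the 8 week intervention".

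**Efficacy.** The abstract places the primary outcome, KOS-ADLS, "at baseline, and at the four, eight and 20 weeks follow-up". Procedures has the questionnaires repeated at weeks 4, 8 and 20 and gives the purpose: "This will allow us to determine if a program leads to a faster recovery and to better long-term effects".

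**Analysis.** The Groups x Time ANOVA covers KOS-ADLS, the VASs and running mileage together. The statistical paragraph also promises to report all dropouts with reasons, with no time limit. It does not carry dropouts forward to the 3-month follow-up, so as not to assume that benefit lasts.

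**The concern.** The efficacy window runs 12 weeks longer than the harms window and the watch window. Two kinds of participant then become hard to recognise at week 20.

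- A runner with a new injury outside the knee after week 8 who still completes the week-20 questionnaires. Under the harms rule as worded, that injury is not counted.
- A runner who has cut back or stopped running after week 8. KOS-ADLS asks about symptoms and limitations in daily activities, so this person can score well and be read as a lasting success.

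The second case bears on the trial's own rationale. The abstract and the discussion both name giving up running as a main consequence of this condition and of running injury. If the long-term comparison does not show who is still running, a favourable week-20 result is open to two very different readings.

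**Working it through.** The plan gives no figure on this point, so the check sets the stated windows side by side.

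| What is recorded | Stated window | Source in the protocol article |
|---|---|---|
| Harms | Course of the programs (8 weeks) | Statistical analyses paragraph; Study design |
| Watch data: mileage, speed, duration, steps | Intervention period (8 weeks) | Procedures; Running mileage |
| KOS-ADLS, VASs | Baseline, weeks 4, 8 and 20 | Abstract; Procedures |
| Running-habits questionnaire | Baseline; repetition not explicit | Procedures |
| Dropouts and reasons | No time limit stated | Statistical analyses paragraph |

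**Step 1: size of the gap.** 20 − 8 = 12 weeks, and 12/20 = 0.60. So 60% of follow-up time has efficacy data but no stated harms or watch record. This is a share of calendar time only.

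**Step 2: does week 20 fill the gap?** Procedures says that the self-report questionnaires from baseline are given again. At baseline it lists a set that includes running habits, then separately attaches the term self-reported questionnaires to KOS-ADLS and the VASs. On the narrow reading, week 20 has no running record. On the broad reading, running habits are asked again. The text does not decide between them. Neither reading extends the harms rule.

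**Step 3: what the week-20 scales can show.** The VASs measure knee pain (usual, worst, and during running). They would show knee symptoms that return, but not a calf or foot injury. The article does not say how running pain is to be scored by someone who no longer runs.

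**Step 4: mileage in the ANOVA.** Mileage is analysed with KOS-ADLS and the VASs, but its stated collection ends at week 8. The week-20 symptom comparison has no matching stated load comparison.

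**Step 5: illustration only.** The documents give no injury rate. Assume a constant hazard and a 20-week risk p of a first new injury, with all 23 runners per arm followed. Risk by week 8 is p8 = 1 − (1 − p)^(8/20). The share after week 8 is (p − p8)/p, and the expected number per arm is 23 × (p − p8). For p = 0.10, p8 = 1 − 0.90^0.4 = 0.0413, the share is 0.0587/0.10 = 0.587, and 23 × 0.0587 = 1.35.

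| Assumed 20-week risk | Expected per arm, weeks 0–8 | Expected per arm, weeks 8–20 | Share after week 8 |
|---|---|---|---|
| 5% | 0.47 | 0.68 | 59% |
| 10% | 0.95 | 1.35 | 59% |
| 20% | 1.96 | 2.64 | 57% |
| 30% | 3.06 | 3.84 | 56% |

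Counts this small can only be described. Even zero events among 23 runners leaves a one-sided 95% upper limit of 1 − 0.05^(1/23) = 12.2%.

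**The case against.** The strongest reply is that this is a condensed article, and that week-20 forms and harms procedures commonly sit in a fuller protocol. That holds for the content of the week-20 form, and it is why the running-habits question is put here as unclear rather than absent. It does not hold for the two windows, because the article states where each one ends.

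Existing safeguards also count. Mileage is logged and analysed through week 8, so running less during the program is visible. Running pain is rated again at week 20. An injury that leads to withdrawal would appear among the dropout reasons, and dropouts are not carried forward. What remains is the participant who is injured elsewhere, or has stopped running, and still answers at week 20.

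A reader might infer three stronger points that the article does not support.

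- *Full training load comes largely after week 8, so harms are watched only while load is low.* The article gives a sequence ("Gradually, running distance will be increased according to symptoms, up to baseline level or more, before adding speed and hills") but no dates, and it describes that sequence as part of the 8-week program. The observed window may therefore include the return to baseline distance.
- *Load transfer from knee to ankle is foreseen.* Ankle forces are listed beside the patellofemoral and tibiofemoral forces, without that rationale.
- *The safety comparison between arms is biased.* No between-arm safety test is planned, and the window is the same in all three arms. What is lost is coverage.

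**Conclusion.** The mismatch is real and rests on the article's own wording: harms and watch data stop with the 8-week programs, while long-term effects are judged at week 20. Over the last 12 of 20 weeks, new injuries outside the knee and reduced or stopped running are not clearly captured in participants who do not withdraw. A good week-20 KOS-ADLS score can then not be separated from improvement in someone who has given up running, unless running habits are in fact asked again.

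The 60% must not be read as the proportion of injuries missed. The 56–59% in the illustration depends on an assumed constant hazard and assumed risks. The point does not affect the week-4 or week-8 results. It limits what can be said about durability and harms after week 8, and it is a low-cost improvement rather than a flaw in the primary analysis.

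**What to change.** 1. Reword the harms rule so that harms, including any new lower-limb injury and its site, are recorded from randomisation to week 20 and reported by arm.
2. At the existing week-20 evaluation, ask for current weekly distance, whether running was stopped and why, and any new injury since week 8. If the running-habits questionnaire is already meant to be repeated then, say so; that would cover the running part but not the harms.
3. Report week-20 KOS-ADLS by arm beside the proportion still running, as description and not as a test.
4. If none of this can be added, limit conclusions on harms and mileage to week 8.

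The cost is a few questions at a contact that already takes place, slightly more burden for participants, and some recall error over 12 weeks. Keeping the watch and online log running to week 20 would reduce recall error in distance but is optional, and uploads after week 8 may be incomplete.

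### The Groups x Time ANOVA does not state that Time is a within-runner factor, and even as a classical repeated-measures ANOVA it suits this visit schedule and attrition poorly

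*Protocol article*

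**What the plan says.** The article names the objective-one test twice. The paragraph on sample size and statistical analyses says "a 2-way ANOVA (Groups x Time) will be used to analyse the effects of the rehabilitation programs on KOS-ADLS, VASs and running mileage", and the Methods/design part of the Abstract uses the same term: "measures of symptoms and functional limitations will be assessed using a 2-way ANOVA (Groups x Time". The Abstract places the primary outcome "at baseline, and at the four, eight and 20 weeks follow-up", and Procedures confirms that the same people are measured again: "self-reported questionnaires completed at baseline will be re-administered". Weekly mileage is logged over the 8-week intervention (Running mileage section).

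The only other model for comparing groups on outcome is conditional. If baseline characteristics differ, "we will adjust group comparisons for confounding variables using an ANCOVA model". That adds covariates and says nothing about the correlation of scores within a runner.

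The same paragraph expects 15% attrition and promises an intention-to-treat analysis of all participants as assigned up to week 8. It rules out carrying dropouts forward to the 3-month follow-up (week 20).

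**The concern.** Groups x Time tests the hypothesis, stated at the end of the Background, that gait retraining brings greater and faster improvement. Its validity and power depend on the error term, which the article does not give. Two readings are possible, and each leaves something to settle.

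- **Literal two-factor ANOVA with one independent residual per score.** Stable differences between runners enter the residual for Groups x Time and hide real differences. The Group test counts four scores from one runner as four runners.
- **Classical repeated-measures ANOVA, the probable intention.** The error terms are right, but the test assumes sphericity across visits separated by 4, 4 and 12 weeks. It also needs a complete set of visits from every runner it includes.

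**Working it through.** **Sample size first.** Inputs from the plan: "α = 0.05, power of 90 % and CID of 13.6 points for the KOS-ADLS, 20 runners are needed in each group (G*Power 3.1.7"), and a baseline SD of 12.9 from the earlier study.

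- Normal approximation for two means: n = 2 × (1.960 + 1.282)² × 12.9² / 13.6² = 2 × 10.51 × 166.4 / 185.0 = 18.9, so 19 per group.
- The exact noncentral t calculation gives 20, the stated figure.
- 20 × 1.15 = 23, as stated.

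The figure comes from a two-group comparison that does not use the repeated scores, so this point leaves it unchanged.

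**Literal reading: why the error terms fail.** Take 3 groups of 20, 4 visits, common SD σ and equal correlation ρ between a runner's visits. The documents give no ρ; 0.3 to 0.7 is assumed.

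- Pooled residual: expected mean square σ², on 3 × 4 × 19 = 228 df.
- Group, under no difference: σ²(1 + 3ρ). The correct error is between runners, 57 df.
- Groups x Time, under no difference: σ²(1 − ρ). The correct error is within runners, 171 df.

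At ρ = 0.5 with σ² = 12.9² = 166.4, the Group mean square averages 166.4 × 2.5 = 416 and the interaction 166.4 × 0.5 = 83, both judged against 166.4. The 5% critical value for 2 and 228 df is 3.035. The Group type I error is therefore roughly P(F > 3.035 / 2.5 = 1.214) = (1 + 2 × 1.214 / 228)^(−114) = 0.30. Dividing instead by 1.9 (ρ = 0.3) and 3.1 (ρ = 0.7) gives 0.20 and 0.38.

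Simulation agrees. Power is for one arm better by 6.8 points at week 4 and 13.6 at weeks 8 and 20 (an assumed profile, SD 12.9):

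| ρ | Group type I, literal | Groups x Time type I, literal | Groups x Time power, literal | Groups x Time power, within-runner error |
|---|---|---|---|---|
| 0.3 | about 20% | about 0.7% | about 56% | about 82% |
| 0.5 | about 30% | about 0.03% | about 50% | about 94% |
| 0.7 | about 38% | under 0.01% | about 39% | about 99.7% |

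With 13.6 points at all three follow-ups (SD 12.4), power is 67%, 64% and 57% literally, against 88%, 97% and 99.9%. At ρ = 0 the two analyses agree, as they should.

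**Probable reading: sphericity.** Under equal correlation the mixed-design ANOVA holds its level (4.8% to 5.2%). If correlation decays with time (0.5 or 0.7 per 4 weeks, assumed) and no correction is made, the Groups x Time type I error is about 6% to 7%.

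**Probable reading: missing visits.** 15% of 69 is 10.35, so about 10 runners may be lost. If they left after week 8, a four-visit analysis restricted to complete runners would discard up to 10 × 3 = 30 observed scores (baseline, week 4 and week 8). Removing those runners sits badly with the promise to analyse everyone as assigned up to week 8.

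**The case against.** The strongest reply is that Groups x Time, for questionnaires given repeatedly to the same runners, is ordinary shorthand for a mixed-design ANOVA. The article states no error term and no independence assumption. It is also a condensed article whose full protocol and analysis plan are not shown, and covariance and sphericity details commonly sit there. This stands. A reader might infer that the plan treats the four scores as independent and that its primary test is therefore invalid. The documents do not support that: the model with one independent residual per score is a reading of the test's name, and the repeated design points the other way.

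It is also true that no conclusion is tied to the Group main effect, so its inflated error rate matters less than the interaction's loss of power. No calculation was made for the VASs or for mileage, which is weekly and not measured at the four visits.

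The authors might run one analysis to week 8 and another for week 20, which would ease the missing-visit problem, but the article does not say so. What survives is that the article fixes a method by name, and that on its probable reading the method is not well matched to uneven visits and expected dropout.

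**Conclusion.** The point holds as a poorly specified and suboptimal choice of primary test, not as a demonstrated wrong analysis. On the probable reading the size is modest: a type I error of about 6% to 7% instead of 5% if correlation decays and no correction is used, plus the loss of about 10 runners from a four-visit analysis if attrition is as expected. The large errors in the table arise only if the test is run literally with independent errors. All error rates rest on assumed correlations, and the power figures also on assumed effect profiles. For any positive equal correlation the direction of the literal-run errors does not change: 1 + 3ρ exceeds 1 and 1 − ρ falls below it.

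**What to change.** In both places where the ANOVA is named, specify instead a linear mixed model for repeated measures with group, visit (categorical) and group x visit, an unstructured within-runner covariance and Kenward-Roger degrees of freedom. Fit it to all observed KOS-ADLS and VAS scores. For weekly mileage, use a mixed model with a runner random effect. Align the sentence on dropouts with this, since the model keeps a runner's earlier scores without needing a week-20 value.

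If ANOVA is kept, the minimum is to state that Time is a within-runner factor and that a Greenhouse-Geisser correction applies. That does not solve the missing week-20 scores.

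The cost is small: a few sentences and a standard procedure, with no new data, visits or runners. Four visits need 4 × 5 / 2 = 10 covariance parameters, which 60 to 69 runners can support. The model relies on dropout being explained by the scores already observed, and the plan should say so.
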